***Allocation, randomization, and blinding of study treatment (intervention):***

***Randomization method:*** A 2 X 2 variable blocked randomization code (ranging between 4 and 8 per block), with stratification by study site and first versus previous episode of wheeze, will be produced by the Drug Development and Innovation Centre at the university of Alberta (DDIC) using random-number generating software. DDIC will produce the study packages, complete the block randomization, and number the bottles. The blinded and numbered study drug packages, in addition to the master code will be available to both study sites if de-blinding is required. Stratification by ‘history of wheeze’ will allow us to track the number enrolled into each sub-group, and ensure we achieve our targeted sample size for each one. We have included children with both first and prior episode of wheeze and powered our study to perform a sub-group analysis for these two groups. Macrolide therapy has been shown to be effective in both bronchiolitis and asthma; incorporating both populations into this study design may provide important insights into how these populations of patients might differ.

Children will be defined as first-time wheezer if they have never had symptoms of wheeze prior to this episode, the symptoms of wheeze have been occurring for < 1 month with no period without resolution of symptoms for greater than 1 week during that 1 month period. Resolutions of symptoms include absence of all respiratory symptoms including wheeze, cough, respiratory distress, and shortness of breath. Some illustrative examples: If the patient has had symptoms for greater than 1 month- these children would be considered a repeat wheezer. If the child has had symptoms of wheezing for 1 month but had a 1 week period without respiratory symptoms in that one month, and we are seeing them after the 1 week resolution period, these children would be also be considered a repeat wheezer. IF the child has had wheezing symptoms for 1 month but was never symptoms free for more than 1 week continuously, this child would be considered a first-time wheezer.

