***Safety monitoring committee and termination policy:*** Adverse events will be actively monitored up to 30 days after the last of Azithromycin was given (day 5). Any child who develops symptoms consistent with adverse effects to azithromycin as evidenced by diarrhea or loose stools, nausea, abdominal pain, and vomiting (common side effects), symptoms of allergic reaction (hives), changes in mood or behaviour, arrhythmia/tachycardia will result in the review of their case by a safety monitoring committee consisting of a pediatric pulmonologist, allergist, and general pediatrician. The committee will review the case and decide whether to break the code and/or terminate the study based on the particulars of the case. If upon review there are concerns about the patient, the code would be broken and the randomization drug discontinued. The panel may consider terminating the study if there are profound adverse effects that would reflect concerns for all children.

***Sample Size and Minimal Clinically Important Difference:*** The telithromycin in acute adult asthma study demonstrated a 50% reduction in asthma symptoms among those using telithromycin (16% asthma symptoms in the placebo group versus 8% in the telithromycin group). We have used this data to estimate the magnitude of effect for our sample size calculations (a 50% decrease in the number of days to symptom resolution). Enrolment of 110 children per treatment arm per first-time versus previous wheeze (total 440), using a one-way ANOVA, will provide 80% power to detect at the .05 level, a 1.18 day

differences in the two treatment groups. This calculation assumes a conservative standard deviation of 6 days in symptoms duration and a 10% loss to follow-up. For the planned sub-group analysis of first-time versus previous wheeze, we have sufficient power to detect a 1.36 day difference between the azithromycin and placebo groups (*Appendix M – Power Calculation*). We think that a reduction in the duration of symptoms by one day or more is likely to be considered meaningful because of its implication for a child missing daycare or school, or parents missing work.

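### The stated detectable differences (1.18 days overall, 1.36 days per wheeze sub-group) do not follow from the stated sample size, SD and loss; the same inputs give about 1.7 and 2.4 days

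*Protocol*

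**What the plan says.** The sample-size paragraph of Protocol section 6 gives these inputs:

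- Size: "Enrolment of 110 children per treatment arm per first-time versus previous wheeze (total 440").
- Test: "using a one-way ANOVA".
- Variability: "This calculation assumes a conservative standard deviation of 6 days in symptoms duration".
- Attrition: "a 10% loss to follow-up".

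From these it concludes that the design "will provide 80% power to detect at the .05 level, a 1.18 day" difference between the two treatment groups. For first-time and previous wheeze separately it adds that "we have sufficient power to detect a 1.36 day difference between the azithromycin and placebo groups", and refers to Appendix M, which is not in the document at hand. It regards a shortening of one day or more as meaningful. It bases the size of effect on a halving of the days to resolution, taken from an adult asthma trial of telithromycin.

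The randomization paragraph of section 6 repeats the sub-group claim: the investigators "powered our study to perform a sub-group analysis for these two groups".

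**The concern.** With 198 evaluable children per arm and an SD of 6 days, the standard error of a treatment difference is 0.60 days. At two-sided 0.05, 80% power needs a difference of about 2.8 standard errors, and 1.18 days is less than 2. The sub-group figure looks worse: half the sample should cost a factor of √2 in the detectable difference, but the stated figure rises by only 15%.

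This paragraph is the only justification given for the size of the trial, and the powered sub-group analysis is one of the reasons given for stratified enrolment. Section 8 also plans to use a negative result to teach community physicians that evidence for antibiotics is lacking. A reader who believes the trial had 80% power near one day may take a null result as excluding a worthwhile benefit, when the design cannot support that reading.

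**Working it through.** **Inputs** (all from the sample-size paragraph). There are 110 children per arm per wheeze stratum, 440 in total, so 220 per arm. After 10% loss, 440 × 0.9 = 396 are evaluable: 198 per arm, and 99 per arm in each stratum. SD is 6 days, power 80%, alpha 0.05. Sidedness is not stated. I take it as two-sided, because the F test of a two-group ANOVA is the two-sided t test, and show one-sided results as well.

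**Formula.** For two groups of n each, the detectable difference is (z₁₋α/₂ + z₀.₈₀) × SD × √(2/n), with z₁₋α/₂ + z₀.₈₀ = 1.960 + 0.842 = 2.802. The table uses the exact noncentral t, which differs by about 0.01 day or less.

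**Attempt to reproduce the plan's figures.**

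- Overall: 2.802 × 6 × √(2/198) = 2.802 × 0.603 = 1.69 days, against 1.18 stated.
- Sub-group: 2.802 × 6 × √(2/99) = 2.802 × 0.853 = 2.39 days (exact t 2.40), against 1.36 stated.

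Dropping the power term gives 1.960 × 0.603 = 1.18, which matches the overall figure. That is the difference detectable with 50% power. It may be the origin of the number, but this is inference. No variant tried gives 1.36.

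**Detectable difference at 80% power under other readings (days)**

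| Reading | Overall | Per sub-group |
|---|---|---|
| Stated in the Protocol | 1.18 | 1.36 |
| Two-sided, 10% loss | 1.69 | 2.40 |
| Two-sided, no loss | 1.61 | 2.28 |
| One-sided, 10% loss | 1.50 | 2.13 |
| One-sided, no loss | 1.42 | 2.02 |
| Four-cell omnibus ANOVA, 99 per cell, same effect in both strata | 2.0 | – |
| Tukey contrast within a stratum, 99 per cell | – | 2.9 |

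**Power at the differences that the Protocol names (two-sided)**

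| Difference | Comparison | With 10% loss | No loss |
|---|---|---|---|
| 1.18 days | Overall | 50% | 54% |
| 1.36 days | Sub-group | 35% | 39% |
| 1 day | Overall | 38% | – |
| 1 day | Sub-group | 21% | – |

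**What the stated figures would require.** At SD 6, 80% power needs about 407 evaluable per arm for 1.18 days (407 / 0.9, so about 453 enrolled per arm) and about 307 evaluable per arm within a stratum for 1.36 days. At the planned numbers after loss, 1.18 days needs an SD of 4.2 and 1.36 days an SD of 3.4. One SD cannot serve both.

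**Consistency of the pair.** At equal power, alpha and SD, halving the sample multiplies the detectable difference by √2 = 1.41, so 1.18 becomes 1.67. The stated ratio is 1.36 / 1.18 = 1.15.

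**Secondary point.** If 1.18 days were the stated 50% decrease, the placebo mean would be 1.18 / 0.5 = 2.36 days. That is hard to square with an SD of 6 and a 21-day diary. The Protocol gives no placebo mean, so the main argument does not rely on this.

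**The case against.** The strongest objection concerns the replacement figures. The values 1.7 and 2.4 belong to simple two-group comparisons. The Statistical Analysis paragraph plans a one-way ANOVA followed, if significant, by Tukey's procedure within each stratum. If that is a four-cell analysis, about 2.0 and 2.9 days apply. This stands as a point of wording: any restated figure must name its test. It also means that 1.7 and 2.4 are lenient to the plan.

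The sub-group sentence claims adequate power without repeating 80%, so the ratio argument and the SD of 3.4 rest on assuming 80% there too. That is fair, but power of 35% to 39% is not adequate by any usual standard, and the randomization paragraph says outright that the sub-groups were powered.

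Appendix M is not available and may use other inputs. If so, the paragraph misreports them; the inputs it prints still cannot give its results. What can be asked is that the two be reconciled.

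The remedy can also be called a design choice, since the investigators could enlarge the trial or defend a smaller SD. Both are open to them. But the Protocol itself calls 6 days conservative, and a smaller SD would have to be justified and still could not produce both figures.

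Finally, a wrong planning figure does not bias the estimate or its confidence interval. That is true; the harm lies in how the trial was justified and in how a null result may be read.

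**Conclusion.** The concern holds. On the printed inputs, with a two-group comparison of means at two-sided 0.05, the trial has 80% power for about 1.7 days overall and 2.4 days within a wheeze sub-group. The stated 1.18 and 1.36 days carry about 50% and 35% power. At the one-day difference called meaningful, the trial would miss a real effect about 62% of the time overall and 79% of the time in a sub-group.

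The result rests on SD 6, 1:1 allocation, equal strata and 10% loss, all from the Protocol, and on two-sided testing, which is assumed. No alternative tried on sidedness, loss or form of ANOVA recovers the stated figures. The statement is wrong as written and must be corrected.

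**What to change.** In the sample-size paragraph:

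- State that 440 enrolled, with 10% loss, SD 6 and two-sided 0.05, give 80% power for a difference of 1.7 days overall and 2.4 days within each sub-group, by a two-group comparison of means.
- If the sub-group tests are adjusted, give the figure for the method used: about 2.6 days with Bonferroni for two sub-groups, or about 2.9 with Tukey over four cells.
- Give the power at 1.18 days (50%) and at one day (38%) for the overall comparison.
- Express the target effect as a difference in days instead of a 50% reduction.

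In the randomization paragraph, withdraw the claim that the sub-groups are powered. Describe them as estimates with confidence intervals, and bring the sub-group wording in the Statistical Analysis paragraph into line. Reconcile Appendix M with the corrected text.

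This costs wording only. The stated figures become less favourable, and no patients are added. If the investigators want to keep 1.18 days with 80% power, they must either justify an SD near 4.2 days or enrol about 453 per arm (about 906 in total).

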#### 6. RESEARCH DESIGN

**Study Overview and Setting:** We propose a two arm, double blind, randomized placebo controlled trial conducted in two urban pediatric emergency departments (Alberta Children's Hospital (ACH), Calgary and Stollery Children's Hospital (SCH), Edmonton). (*Appendix A – Study Design Schema*)

**Patient recruitment:** Starting January, 2010, trained research assistants will be on-call 16 hours per day, seven days per week (*Appendix B – Emergency Medicine Research Associates Program*). The triage nurse will notify on-call research assistants about children 12-60 months of age who present with wheeze during the study period. Written, informed consent will be obtained as follows: 1) a video of a primary investigator explaining the study will be played for the parent (or legal guardian) by the assistants, 2) a primary investigator or senior research coordinator will be available by telephone to answer any questions the parent/legal guardian might have about the study 3) the research assistant will ask the parent/legal guardian who have verbally agreed to participate to sign the written consent form (*Appendix C – Consent Form*). A more lay description of the study including rationale, objectives and the study commitment will also be distributed as a brochure.

We propose to implement a lottery remuneration process within the ED. For each individual screened, the research assistant, admitting clerk, the nurse facilitating the enrollment visit can complete a ballot for entry. The ballot will contain the patient's bed number, time and date of the patient encounter. RA will check the handed ballot. The entry for RA will be confirmed through check box. The lottery draw will be completed after every 1000 entries. The winner will receive a Safeway Gift card for \$500.

**RMO Database:** We will maintain a database for eligible individuals who refuse, are missed, or are otherwise excluded to assess the generalizability of our study sample.

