**Statistical Analysis:** The baseline variables in the two groups will be compared overall and by enrolment center in terms of means, standard deviation, and range, and as appropriate, median, inter-quartile range, percentages and 95% confidence intervals. Imbalances between treatment groups for key baseline variables such as age, gender, duration of illness, presence of atypical bacteria, use of ICS or oral corticosteroids, and baseline clinical severity will indicate the need for an adjusted analysis. We will also include an interaction term in the analysis (drug X presence or atypical bacterial infection) to determine if azithromycin has a different degree of effectiveness among those with atypical bacteria present. Furthermore, for each response variable, we will perform an exploratory adjusted analysis incorporating enrolment center as a factor to ensure that unmeasured differences between enrolment centers do not bias our results. The primary outcome, time to symptom resolution, will be assessed for normality of distribution by the Wilk Shapiro Test and, if necessary, will be transformed to yield suitable distributions or Kruskal Wallis (non parametric ANOVA analogue) will be used to test the main hypothesis. If the one way ANOVA is significant, then, a-priori decided comparisons (placebo versus azithromycin in first-time wheezing children and placebo versus azithromycin in children with a prior wheeze history) will be tested via Tukey's Honest significant differences procedure. If an adjusted analysis is necessary, we will use an Analysis of Covariance model incorporating those baseline factors which are imbalanced between treatment groups and any other variable that is thought to be of clinical relevance. An adjusted analysis will be performed in the event that co-intervention numbers (such as ICS or oral corticosteroid use) between the groups are not comparable. We also plan to perform a sub-group analysis to detect clinically significant differences in the each of the two wheezing sub-groups. Linear regression will be used to analyze  $\beta$ -agonist use during the 21 day follow-up period and Cox regression modelling will be used to analyse the time to next disease exacerbation.

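### Site, a stratification factor, enters only an exploratory analysis; other covariates are picked from observed imbalance, and no rule says which result decides

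*Protocol*

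**What the plan says.** Protocol section 6, Randomization method, describes a blocked allocation "with stratification by study site and first versus previous episode of wheeze". There are two sites: the trial is a "randomized placebo controlled trial conducted in two urban pediatric emergency departments".

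The Statistical Analysis paragraph of the same section does four things with covariates.

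- Site: "we will perform an exploratory adjusted analysis incorporating enrolment center as a factor", for each response variable.
- Baseline variables: "Imbalances between treatment groups for key baseline variables such as age, gender, duration of illness", together with atypical bacteria, corticosteroid use and baseline clinical severity, are what call for an adjusted analysis. No size of imbalance is given.
- Content of that analysis: an ANCOVA "incorporating those baseline factors which are imbalanced between treatment groups and any other variable that is thought to be of clinical relevance".
- Co-interventions: "An adjusted analysis will be performed in the event that co-intervention numbers (such as ICS or oral corticosteroid use) between the groups are not comparable".

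The main test is a one-way ANOVA, but after a normality check the outcome "if necessary, will be transformed to yield suitable distributions or Kruskal Wallis (non parametric ANOVA analogue) will be used to test the main hypothesis". A significant ANOVA is followed by planned treatment comparisons within first-time and within repeat wheezers. The paragraph does not say which result counts if the unadjusted and adjusted analyses differ.

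**The concern.** An analysis should follow the randomization. A factor on which allocation was balanced belongs in the main model; otherwise the standard error does not reflect the balance that the design has bought.

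The second issue is how the remaining covariates are chosen. In a randomized trial, baseline imbalance is chance. The reason to adjust for a variable is that it predicts the outcome, and that can be decided beforehand. Under the stated rule, a prognostic variable that happens to be balanced is left out and its precision is lost, while an unimportant one that happens to be imbalanced goes in.

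The co-intervention trigger goes further. The Co-Interventions paragraph lets physicians prescribe corticosteroids freely and records medication at enrolment and during follow-up, so the trigger can bring post-randomization treatment into the model. Such treatment may respond to the study drug. The diary's red-star category is itself partly defined by oral corticosteroid treatment, so adjusting for later steroid use could remove part of the effect being measured.

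Finally, with several permissible models and no stated order, more than one primary p-value is available.

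**Working it through.** **Inputs from the protocol.** 110 children per arm in each wheeze group, so 220 per arm; 10% loss, so 220 × 0.9 = 198 per arm; SD 6 days; 0.05 level, taken as two-sided because the protocol does not say; two sites. The protocol gives no between-site difference and no proportion of variance explained (R²). Both are assumptions below, shown as ranges.

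**The plan's own power figure.** The standard error of the treatment difference is 6 × √(2/198) = 0.603 days. Power for the stated 1.18 days is Φ(1.18/0.603 − 1.96) = about 50%, not 80%; with 220 per arm it is 54%. The difference that has 80% power at 198 per arm is (1.96 + 0.84) × 0.603 = 1.69 days. This discrepancy is a separate matter and the present point does not rest on it, but gains in power have to be shown from both starting values. All figures are for a two-arm comparison of means.

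**Leaving out site.** For two equal sites whose means differ by d days, R² = (d/2)²/36. Putting site in the model multiplies the standard error by √(1 − R²). A test that ignores site has true alpha 2 × [1 − Φ(1.96/√(1 − R²))].

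| Assumed site difference (days) | R² | True alpha, site omitted | Power for 1.69 days, site included (80.0% without) |
|---|---|---|---|
| 0.5 | 0.2% | 0.0498 | 80.1% |
| 1 | 0.7% | 0.0492 | 80.3% |
| 2 | 2.8% | 0.0468 | 81.1% |
| 3 | 6.3% | 0.0429 | 82.5% |

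**Pre-specified prognostic covariates.** The same formula applies, with power = Φ(difference/(0.603 × √(1 − R²)) − 1.96).

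| Assumed R² | Fall in standard error | Power for 1.69 days (from 80%) | Power for 1.18 days (from 50%) |
|---|---|---|---|
| 5% | 3% | 82% | 52% |
| 10% | 5% | 84% | 54% |
| 20% | 11% | 88% | 59% |
| 30% | 16% | 92% | 65% |

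**How often the imbalance trigger fires.** The protocol names six key variables as examples. If they are independent and imbalance means p < 0.05 (an assumption, since no threshold is set), at least one is imbalanced by chance in 1 − 0.95⁶ = 26% of trials.

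**What the open choice does to type I error.** Simulation with 396 children, no treatment effect, six independent covariates of equal strength, imbalance at p < 0.05, and 5,000 runs (simulation error near 0.05 is √(0.05 × 0.95/5000) = 0.003):

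| Analysis reported | Joint R² 10% | Joint R² 30% |
|---|---|---|
| Unadjusted | 0.052 | 0.053 |
| Imbalance-selected | 0.048 | 0.045 |
| All six, pre-specified | 0.052 | 0.052 |
| Best of the three | 0.068 | 0.082 |

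**The case against.** The strongest reply is that the protocol assigns the ANOVA or Kruskal-Wallis test to the main hypothesis and calls the centre analysis exploratory. A sympathetic reader would take the unadjusted test as primary and the ANCOVA as support. Candidate covariates are named, and the imbalance threshold and final list could sit in a statistical analysis plan that is not shown. That reading is possible, but the text does not state it: the paragraph makes adjustment necessary once imbalance is seen, and gives the resulting ANCOVA no secondary status. The protocol also sets the selection rule itself, so the objection is to a stated rule and not to missing detail.

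Four stronger readings are tempting, and the documents do not support them.

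- *Both stratification factors are ignored.* The sample size is built on arm by wheeze group and the planned comparisons are made within wheeze group, so wheeze history apparently defines the ANOVA groups. Only site is left out.
- *The test becomes badly conservative, with a true size of 3.9% or 2.8%.* Those sizes need a factor that explains 10% or 20% of variance. For site this means a difference of 2 × 6 × √0.10 = 3.8 days or 2 × 6 × √0.20 = 5.4 days, well beyond the 1.18-day treatment difference. Nothing in the protocol suggests it.
- *The trial's power would rise from 80% to 84–88%.* That holds only for a difference that truly has 80% power, about 1.69 days, and not for 1.18 days.
- *Choosing covariates by imbalance inflates type I error.* Applied mechanically it does not. Inflation needs a free choice among results, which the protocol does not propose but also does not rule out.

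It is also fair to say that the protocol gives no evidence on how prognostic severity or duration of illness is, and that √(1 − R²) is a linear-model result. It does not carry over directly to the Kruskal-Wallis option or to a time-to-event model.

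**Conclusion.** The point holds in a limited form and is worth acting on. The omission of site is a real mismatch with the randomization, but it is small and errs on the conservative side across the assumed site differences. The larger loss is the precision given up by not fixing prognostic covariates in advance; how large depends on an R² that the documents do not give.

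The imbalance and co-intervention triggers are poor grounds for adjustment whatever the R². The missing statement of which result decides is the part that could affect the credibility of a positive finding: the error rate stays near 5% if one model is fixed, and is about 0.07 to 0.08 only if the most favourable of three may be chosen. None of this invalidates the trial or shows that the planned main test is anti-conservative.

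**What to change.** In the Statistical Analysis paragraph, name one primary model for time to symptom resolution, containing treatment, site, wheeze history, baseline clinical severity and duration of illness at enrolment, and say that its treatment estimate decides. If the final outcome model is not a linear one, carry the same terms over as strata or covariates.

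Delete the imbalance trigger, the co-intervention trigger and the allowance for any further variable. Label the unadjusted comparison and every other adjusted model as sensitivity analyses. Co-intervention use can still be described by arm.

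The change is to wording and needs no more children. Site, wheeze history and duration of illness are already part of the plan. Baseline clinical severity is named as a key variable, but the visible text defines no scale for it and the data forms are not shown, so the sponsor should confirm which recorded measure is meant and write it in.

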#### 5. HYPOTHESES

**Primary Hypothesis:** Treatment of pre-school children with an acute episode of wheezing symptoms with 5 days of azithromycin will resolve their symptoms sooner.

**Secondary Hypotheses:** Treatment of pre-school children with acute wheezing symptoms with 5 days of azithromycin will: a) cause these children to use less rescue  $\beta_2$  agonists than those treated with placebo; and b) allow these children to remain free of subsequent wheezy episodes longer than those treated with placebo.

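### The primary test is a one-way ANOVA whose groups are not defined; on its most natural four-cell reading it does not isolate the drug effect, and no overall azithromycin-versus-placebo test is named

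*Protocol*

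**What the plan says.** Protocol section 5 (Hypotheses) gives a single primary hypothesis, not restricted by wheeze history: "Treatment of pre-school children with an acute episode of wheezing symptoms with 5 days of azithromycin will resolve their symptoms sooner". Section 6 (Research Design) describes the design as follows: "We propose a two arm, double blind, randomized placebo controlled trial". Randomisation is "with stratification by study site and first versus previous episode of wheeze".

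The Sample Size paragraph reads "Enrolment of 110 children per treatment arm per first-time versus previous wheeze (total 440), using a one-way ANOVA, will provide 80% power". It then attaches that power to a difference of 1.18 days between the two treatment groups, and gives a separate figure of 1.36 days for the analysis by wheeze history. It assumes an SD of 6 days and 10% loss to follow-up.

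The Statistical Analysis paragraph says that the main hypothesis will be tested by one-way ANOVA, or by Kruskal-Wallis if the data are not normal. It continues: "If the one way ANOVA is significant, then, a-priori decided comparisons (placebo versus azithromycin in first-time wheezing children", and likewise for children with a prior wheeze history, "will be tested via Tukey's Honest significant differences procedure". Analysis of covariance is used only if there is imbalance, and the centre-adjusted analysis is exploratory. A further sub-group analysis in the two wheeze groups is mentioned without a method.

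**The concern.** The hypothesis is about one contrast, azithromycin against placebo. The test named for it is an omnibus test whose groups are not listed. If the groups are the four combinations of arm and wheeze history, the null hypothesis is that all four means are equal. Rejecting it does not say that the drug works, because a difference between first-time and previous wheezers is enough to reject it. Conversely, three degrees of freedom are spent on a one-degree-of-freedom question, which costs power when the drug effect is similar in both strata.

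The drug comparisons that are named sit within strata and behind this gate. No overall drug-versus-placebo comparison is specified, and there is no rule for the case where the ANOVA is significant but neither within-stratum comparison is. At stake is whether the trial can declare its primary hypothesis met or not met.

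**Working it through.** **How many groups does the ANOVA have?** Two pieces of text point to four: the trial is sized at 110 per arm per history group under a one-way ANOVA, and Tukey comparisons inside each stratum need four cell means. Two point to two: the design is two-arm, and the 1.18-day target is described as a difference between the two treatment groups. With two groups, however, the Tukey step does not follow from the ANOVA, because its within-stratum comparisons are not between that ANOVA's groups. The text therefore needs correcting on either reading.

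**Inputs.** SD 6, alpha 0.05 and 10% loss are from the Sample Size paragraph: 110 × 0.9 = 99 per cell, 198 per arm, 396 in all. The effect of history on symptom duration is not given anywhere; 1 to 3 days is an assumed range.

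**The protocol's own figure.** The two-sided detectable difference with 80% power is (1.960 + 0.842) × 6 × √(2/n). For n = 198 per arm this is 1.69 days; for n = 220 it is 1.60. The stated 1.18 days is not reproduced and has about 50% power with 198 per arm. That is a separate matter, and Appendix M (the power calculation) is not at hand. Both 1.18 and 1.69 days are used below.

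**Four-cell omnibus F (3 and 392 df, critical value 2.63).** The noncentrality is λ = nΣ(μᵢ − μ̄)²/σ². For a history difference h and a uniform drug effect d, the four means lie at ±h/2 ± d/2, so

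λ = 99 × 4 × (h²/4 + d²/4) / 36 = 2.75 (h² + d²).

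The two effects enter in the same way, so the test cannot tell them apart. The direct 1-df contrast (critical value 3.87) has λ = 2.75 d², free of h.

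No drug effect (d = 0):

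| h (days, assumed) | λ | P(omnibus significant) |
|---|---|---|
| 1 | 2.75 | 25% |
| 1.5 | 6.19 | 53% |
| 2 | 11.0 | 80% |
| 3 | 24.75 | 99% |

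The direct contrast rejects in 5% throughout.

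Uniform drug effect, no history difference (h = 0):

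| d (days) | λ | Omnibus | Direct 1-df |
|---|---|---|---|
| 1.18 | 3.83 | 34% | 50% |
| 1.69 | 7.85 | 64% | 80% |
| 2.0 | 11.0 | 80% | 91% |

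With d = 1.69 and h = 2, λ = 2.75 × (2.856 + 4) = 18.85 and the omnibus test is significant in about 97%. Of that λ, 11.0 comes from history and 7.85 from the drug.

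**Gate followed by Tukey (simulation, 100,000 trials per scenario).** Tukey's critical value on the t scale is q/√2 = 3.649/√2 = 2.58.

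- No drug effect: at least one false within-stratum drug finding in 1.8% with h = 0, and about 2% with h = 2 or 3.
- No drug effect, h = 2: the ANOVA is significant and neither drug comparison is in 78% of trials.
- d = 1.69, h = 0: at least one within-stratum comparison significant in 47%.

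**Cost of Tukey for two planned comparisons.** Tukey covers six pairs among four cells. Bonferroni for two needs 2.24. The standard error within a stratum is 6 × √(2/99) = 0.853 days. The difference detectable with 80% power is then (2.58 + 0.84) × 0.853 = 2.92 days with Tukey, and (2.24 + 0.84) × 0.853 = 2.63 days with Bonferroni.

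**The case against.** The strongest reply is that the protocol never says the ANOVA has four groups. It calls the trial two-arm, ties its main powering target to the two treatment groups and treats the wheeze-history comparison as a separate sub-group analysis. If the ANOVA has two groups, it is itself the direct test, and with allocation stratified by history a history difference cannot drive it. This stands as a statement of the ambiguity. It does not rescue the text, because the Tukey step then has no ANOVA to follow.

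A reader might infer that azithromycin is never compared with placebo. That is too strong: both planned comparisons do so, one in each stratum, and a further sub-group analysis is mentioned without a stated gate. What is missing is the overall comparison.

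A reader might also infer that a history difference produces false claims of drug benefit. It does not if the procedure is followed to its end, since false within-stratum findings stay at about 2%.

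The two harms also rest on opposite assumptions about one unknown. The gate opens wrongly when history matters, and it loses most power when history does not matter. They should not be added together.

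Finally, Tukey for two comparisons is conservative but valid. A follow-up method after Kruskal-Wallis and a drug-by-history interaction are details that a statistical analysis plan can settle, and their absence here is not a finding.

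**Conclusion.** The point holds in this form. The primary test's groups are undefined, and the sample-size and analysis paragraphs pull towards different readings. On the more natural four-cell reading, the test does not isolate the drug effect, and no overall azithromycin-versus-placebo test is named.

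The harm is a main test that can be positive for reasons unrelated to the drug, and a loss of power when the benefit is uniform and history has little effect. At 1.69 days that loss is 16 percentage points at the gate (80% to 64%), and 33 points if at least one Tukey comparison must also be significant (80% to 47%). A history difference restores the power of the gate but not the meaning of its result.

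These sizes rest on the four-cell reading, 99 evaluable children per cell, a common SD of 6 days and, for the false-opening figures, an assumed history difference of 1 to 3 days. Because this is the confirmatory test of the primary outcome, it should be corrected before any unblinded analysis.

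**What to change.** State the primary test as the 1-df azithromycin-versus-placebo effect on time to symptom resolution in all randomised children, stratified by or adjusted for wheeze history and site. If the data are not normal, use a rank-based stratified equivalent such as the van Elteren test.

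Remove the omnibus ANOVA gate. Keep the two planned within-stratum comparisons, tested with Holm or Bonferroni for two in place of Tukey, and say that they support the overall test and do not replace it.

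Bring the Sample Size paragraph into line by naming the same test and the number of groups it compares.

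The cost is wording in the protocol and in any statistical analysis plan. No extra children, visits or data are needed, and under a uniform drug effect the same data give a more powerful test.
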